# Protocol for a pilot cluster randomised controlled trial of PRoGRAM-A (preventing gambling-related harm in adolescents): a secondary school-based social network intervention

**DOI:** 10.1186/s40814-024-01537-w

**Published:** 2024-08-13

**Keywords:** Gambling-related harms, School intervention, Cluster randomised trial, Process evaluation, Adolescent, Peer-supporters, Social network analysis, Message diffusion

## Abstract

**Background:**

In the UK, recent evidence of young people and gambling indicates a higher prevalence of gambling in comparison to other addictive behaviours. Engaging in gambling-related behaviour at a young age is associated with short and long-term consequences, including financial, emotional, academic, interpersonal, and physical and mental health detriments; otherwise known as gambling-related harms (GRH). Given the unique vulnerability of this younger group, early interventions aimed at delaying or preventing gambling are critical. PRoGRAM-A (Preventing Gambling-Related Harm in Adolescents) is a school-based, social network intervention to protect young people from future GRH, by delaying or preventing gambling experimentation.

**Methods:**

Pilot cluster RCT with an embedded process evaluation and health economic scoping study.

**Participants:**

PRoGRAM-A will be delivered in four schools, with two control schools acting as a comparator. All are secondary schools in Scotland. Baseline surveys were conducted with students in S3 (ages 13–14). Follow-up surveys were conducted with the same cohort, six months post-baseline.

**Intervention:**

PRoGRAM-A trainers will deliver a 2-day, out-of-school training workshop to Peer supporters. Peer supporters will be nominated by peers among their school year group (S3, age 13–14). Workshops will provide peer supporters with information on four gambling-related topics: (1) what is gambling? (2) gambling and gaming, (3) gambling marketing, (4) identifying harm and reducing risk. Peer supporters will disseminate the information (message diffusion) they have learned among their friends and family over a 10-week period. After the 2-day workshop, PRoGRAM-A trainers will conduct × 3 in-school follow-up sessions with peer supporters to offer support, encouragement, and advice to Peer Supporters as well as monitor and explore the extent of their message diffusion.

**Primary outcome:**

The primary outcome of the pilot cluster RCT (cRCT) will be whether progression to a phase III RCT is justified.

**Discussion:**

This will be the first pilot cluster RCT (cRCT) of an intervention to prevent gambling-related harms among young people within the UK. If findings indicate feasibility and acceptability, funding will be sought for a phase III RCT of effectiveness.

**Trial registration:**

Researchregistry8699. Registered 21^st^ February 2023.

**Supplementary Information:**

The online version contains supplementary material available at 10.1186/s40814-024-01537-w.

## Background

Globally gambling is increasingly recognised as a public health concern [1]. The last two decades have witnessed the transformation of the commercial gambling market, with rapid technological advances creating greater opportunity (and ease) to gamble anywhere and anytime. Running parallel to this is the growth of sophisticated and tailored gambling marketing strategies to promote gambling products to consumers. The rapid growth of the gambling industry has been accompanied by a rise in gambling harm, with an estimated six people affected for each person experiencing gambling harm [2].

In response to these associated harms, most countries do not allow children and young people under the age of 18 to engage in commercial forms of gambling [3]. However, children and young people are still exposed to gambling marketing, of which advertising is a key component. A recent UK study reported that 96% of 11–24-year-olds had been exposed to gambling advertising over the last month [4]. A further concern is the intersection of digital gaming and gambling, which has led to young people being increasingly exposed to ‘gambling adjacent’ activities, such as loot boxes, skin betting, social casino games, and sponsorships of e-sports teams by major gambling companies [5]. Despite UK regulatory boards excluding gambling adjacent activities from the definition of gambling [6], young people often identify that they do in fact qualify as gambling [5]. Evidence further suggests that young people who engage in ‘gambling adjacent activities’ are at a greater risk of problematic gambling behaviour [7].

This increased exposure to gambling-related marketing, along with the rise of online forms of gambling has contributed to the normalisation of gambling behaviour within the everyday lives of children and young people. It is, therefore, not surprising that recent systematic reviews of interventions to prevent gambling harm have highlighted children and adolescents as a key priority group and recommend the introduction of more theoretically informed, school-based gambling education programmes, with long-term follow-up [8–10].

In the UK, recent evidence of young people and gambling indicates a higher prevalence of gambling in comparison to other addictive behaviours. For example, a 2022 report conducted by the Gambling Commission found that 50% of 11–16-year-olds have taken part in some form of gambling over the past 12 months, in comparison to drinking alcohol (41%), using e-cigarettes (17%), smoking tobacco cigarettes (7%), or using illicit drugs (5%) [11]. While the incidence of problematic gambling within this age group remains relatively low (0.9%), young people who have taken part in some form of gambling over the past 12 months are more likely to engage in co-occurring risk-taking behaviours, such as alcohol consumption (54%), e-cigarettes and vaping (32%), cigarette smoking (17%), and illicit drug use (16%) [11]. Engaging in gambling-related behaviour at a young age is associated with short and long-term consequences, including financial, emotional, academic, interpersonal, and physical and mental health detriments [2–5]; otherwise known as gambling-related harms (GRH) [12]. Moreover, GRH incurs a considerable economic burden, with a 2023 evidence review by Public Health England reporting the overall economic cost of problem gambling, in the UK, to be between £1.05 and £1.77 billion and the estimated health-related costs to be between £635 and £1355 million [13].

While early intervention programmes exist within public health policy for tobacco, alcohol, and drugs, parallel programs for gambling, separate from industry influence, are lacking. Given the unique vulnerability of this younger group, early interventions aimed at delaying or preventing gambling are critical. This has led to calls for robust, independent early intervention to protect young people from future GRH, by delaying or preventing gambling experimentation [4, 14, 15]. To address this gap, the lead author (FD) obtained funding from the Medical Research Council (MRC) Public Health Intervention Development (ref: MR/S019200/1), to adopt an existing anti-smoking intervention called ASSIST (A Stop Smoking in Schools Trial) that has been successful in protecting young people from smoking harm [16]. This funding supported the development of PRoGRAM-A (Preventing Gambling-Related Harm in Adolescents) and a small feasibility study, which took place in one secondary school between August–November 2021. This protocol paper presents the next phase of PRoGRAM-A’s development—a pilot cluster randomised control trial (RCT). The protocol (current version PRoGRAM-A protocol V2.0 07Aug 2023) is reported using the SPIRIT guidelines [17], with the completed checklist added in Additional file 1: Table S1.

## Methods

### Research aim and research questions

The overall aim is to conduct a pilot cluster randomised control trial (cRCT) of a gambling prevention intervention among young people aged 13–15 to determine the utility of conducting a Phase III RCT assessing effectiveness and feasibility. This aim is unpacked via a series of research questions.

#### Recruitment and randomised trial delivery

Can a sufficient number of schools and students be recruited, randomly allocated, and retained?How can the collection of baseline and follow-up data be optimised?What gambling prevention activities occur in control schools and how is the impact perceived?Following the pilot cluster RCT (cRCT), is a phase III cRCT justified in relation to our progression criteria?

#### Acceptability, feasibility, and fidelity of intervention delivery

5)Is it feasible and acceptable to implement the intervention in four schools?6)What do qualitative and quantitative data suggest in terms of refinements to programme theory, implementation, fidelity, reach, scalability, and acceptability?7)Are there potential harms and unintended consequences of the intervention? How might these be reduced? How can these be measured?8)What characteristics are associated with being nominated as a peer supporter?9)What is the potential and actual extent of message diffusion in peer supporter networks and to whom and why?10)What contextual factors influence message diffusion (e.g. size of student networks, where, when, and how conversations are initiated, what communication methods are used, what is discussed? level of peer supporter confidence)11)What are the key issues to consider to support future scalability?12)What are the direct implementation costs associated with delivering PRoGRAM-A?13)What economic measures are appropriate and available for use in a future health economic evaluation as part of a definitive cRCT?

### Pilot cRCT

PRoGRAM-A is an 18-month, two-arm, pilot cluster RCT with an embedded process evaluation which includes a social network analysis and health economic feasibility study, conducted in six schools in Scotland. Following the completion of a baseline student survey assessing gambling attitudes, awareness, and behaviour, four schools will be randomised to receive the intervention (PRoGRAM-A) and two will continue with usual practice. The two comparator schools have been included to test the acceptability of randomisation. Key phases of the study are outlined in Fig. 1.

**Fig. 1 Fig1:**
[figure not shown]
PRoGRAM-A flow diagram

### Setting, inclusion/exclusion criteria

Setting is any state-funded secondary school in Scotland. Inclusion criteria are students in S3, aged 13–15, (equivalent to years 9 and 10 in England, Wales, and Northern Ireland) who give their assent to participate in the study. The exclusion criteria are (1) schools for young people with special needs, (2) residential schools, (3) students who do not provide assent, (4) student’s parent/carer who opt their child out of the study or do not give consent for peer supporter training, and (5) schools who do not consent to participate.

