### Recruitment

Schools will be invited to take part in an online information webinar where they can find out more about PRoGRAM-A and what taking part in the pilot RCT would involve. This will help schools make an informed decision about whether they would like to volunteer to take part or not. The school’s webinar invitation will be circulated via existing networks from the research team. This includes dissemination via two voluntary sector organisation (Fast Forward and Larkhall Universal Connections) that have delivered existing gambling prevention work in several schools throughout Scotland. At this pilot stage, there is no restriction on school location, with any state-funded school in Scotland eligible to express interest in taking part.

After the webinar, schools who are interested in finding out more information will email a member of the research team. Depending on the number of schools that express an interest, a purposive sampling frame may be applied to ensure diversity in terms of school size and location. Schools that opt in to PRoGRAM-A will then receive a site visit from a member of the research team where they will be given a more detailed briefing about what is involved and have the opportunity to ask questions. After this site visit, and if they still want to proceed, the school will be registered into the pilot RCT.

Students will be given an information letter about the survey at least 1 week prior to data collection and an oral description of the study from school teachers. Students will have the opportunity to ask questions before deciding whether they want to take part or not. On the day of data collection, students will be invited to give signed assent to participate in data collection. In advance of data collection parents/guardians will be sent an information letter telling them about the research study and giving them an opportunity to opt their child out if they do not want them to participate.

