### Randomisation

Schools will be randomised using a remote system set up by Edinburgh Clinical Trials Unit in order to conceal the allocation sequence. The allocation sequence will be stored on a secure server and concealed from all personnel involved in the trial. It will be created, using computer-generated pseudo-random numbers, by a clinical trials unit member of staff with no link to, or contact with, any of the participating schools. The randomisation will be stratified by school size (less than 200/greater than or equal to 200 students on the 3rd year school roll). The PRoGRAM-A intervention to comparator group randomisation ratio within each stratum is 2:1.

Once all schools have been identified, confirmed they wish to take part, and baseline forms have been completed, a designated member of the trial team will contact the Edinburgh Clinical Trials Unit (ECTU) data management team requesting the randomised assignment of all schools. These assignments will then be communicated to the schools by the trial team member. Prior to baseline form completion all trial team members, schools, and students will be blinded; after this point, all will be unblinded.

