What Procedures	PRoGRAM-A is a peer-led gambling prevention programme for S3 students. Students will complete a peer nomination questionnaire, nominating those within their year group they respect or look up to. The students with the highest number of nominations will be invited to be peer supporters. At the time of peer nomination, students are not aware that they are identifying influential others in a gambling-related context to prevent biased nomination. Peer supporters undergo 2 days of training covering: (1) what is gambling; (2) gambling and gaming; (3) gambling advertising and marketing; (4) gambling-related harm and keeping safe. They learn how to have informal conversations with anyone in their social network about these topics. These conversations aim to spread new social norms throughout their network and community. After the initial training, the trainers will meet with the peer supporters at three follow-up sessions over the next 8 to 10 weeks to check their progress and to maintain engagement
Who provides	Implementation of the intervention including the 2-day training and the follow-up sessions will be provided by trainers from ‘Evidence to Impact’—a social enterprise that specialises in translating public health into practice. They will be supported by the research team and school staff to arrange suitable times/accommodations for the training and to gather pupils together for the follow-up sessions as well as the interviews and focus groups as part of the process evaluation (all during school hours). Two members of the teaching staff will accompany the peer supporters to the training venue—they will not be involved in the training. They will act as chaperones and will only be called upon if pupil behaviour becomes challenging
How	Each school will identify a main point of contact within the school for the study. The research team will liaise with the school and the trainers to identify and book a suitable training venue as close to the school as possible (ideally walking distance). Transport, if required, will be organised by the research team and trainers with input from the schools. The school will identify staff to accompany the students to the venue and to act as chaperones for the 2 days. The research team will also liaise with the school (and trainers) to book class space and time for the peer supporters to attend the three follow-up sessions and any interviews/focus groups that students are invited to take part in

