#### Assessment and follow-up

Baseline data collection will be conducted before the randomised allocation to PRoGRAM-A or control is revealed to schools. A baseline assessment will be completed in the first term of school with a follow-up survey six months later. Given the logistical challenges of conducting fieldwork in schools, data collection will be paper-based, ideally conducted under exam conditions via a special assembly. Students will be reassured that completing the survey will be completely confidential and anonymous with their name not attached to the survey. Members of the research team and class teachers will be present to help administer the survey, answer any questions students may have, and also support students with additional needs.

Peer supporters will receive three follow-up visits from the trainers. Conducted in school these visits will collect data on the extent of message diffusion among their social network, reinforce key messages, and address any questions or challenges peer supporters may have. Trainers will record any unintended consequence either through observation or direct feedback from school staff and students.

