## Strengths and limitations

A key strength of this pilot RCT is its randomised design, stratification by school size, and its delivery in secondary schools which is a replicable and scalable setting for population-wide intervention delivery. Further, the preceding development study (ASSIST) created links with local and national governments as well as the education, public, and voluntary sectors which can help to facilitate the future rollout of PRoGRAM- across schools in the UK, should findings from the proposed pilot study support a definitive trial. Finally, PRoGRAM-A has the potential to be cost-effective (a key factor in scalability and translation) due to reliance on social capital and spreading information through social networks thus maximising reach and potential effectiveness [17].

However, there are three key limitations. The small number of pilot schools makes it difficult to pilot different combinations of school variables such as schools in urban/rural areas and schools in deprived/affluent areas. Next, whilst a lot of the delivery costs will be ‘in kind’ contributions rather than an actual financial payment, funding will be required to support the delivery of PRoGRAM-A (e.g. payment of youth worker time, venue hire, and catering costs for peer supporter training) and quality assessment to maintain intervention delivery integrity. Finally, despite a key strength of PRoGRAM-A being its peer approach (with students nominated by their peers, as opposed to teachers), once a peer-supporter is nominated they may choose to either accept or decline the role. The option for students to revoke their participation could result in the effects of attrition bias as more confident, outgoing students may self-select to remain, while more introverted students may choose to decline. However, this has never been reported in ASSIST or any other adaptations to the programme. In order to combat the potential effects of sampling and attrition bias, the study population will be continually monitored and discussed with the research team in order to control for any unintended effects.

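### As worded, exclusion criterion 4 bars students from the whole study when a parent refuses only the peer-supporter training, a refusal that can arise only in intervention schools

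*Protocol article*

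**What the plan says.** The section on setting and inclusion/exclusion criteria gives one list for the study. Students in S3 are included if they are those "who give their assent to participate in the study". The fourth exclusion concerns parents or carers who "opt their child out of the study or do not give consent for peer supporter training". The two limbs are joined by a plain alternative and share one consequence.

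Other sections bear on how the second limb would work:

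- **Pilot cRCT:** after the baseline survey, "four schools will be randomised to receive the intervention (PRoGRAM-A) and two will continue with usual practice".
- **Assessment and follow-up:** "Baseline data collection will be conducted before the randomised allocation to PRoGRAM-A or control is revealed to schools".
- **Randomisation:** "Prior to baseline form completion all trial team members, schools, and students will be blinded; after this point, all will be unblinded".
- **Table 1, What Procedures:** "The students with the highest number of nominations will be invited to be peer supporters". No number or percentage is given.
- **Recruitment:** before data collection, parents receive a letter "giving them an opportunity to opt their child out if they do not want them to participate". Students then give signed assent on the day. Consent for training is not mentioned as a condition of being surveyed.
- **Strengths and limitations:** "once a peer-supporter is nominated they may choose to either accept or decline the role". Refusal is raised there as a possible source of attrition bias.

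**The concern.** Eligibility for the study and eligibility for the peer-supporter role are different things, and criterion 4 merges them. A parent in a control school has no training to refuse, so the second limb can take effect only in intervention schools, and there only among the students their peers nominate most. If it were applied as written, well-nominated students would leave one arm while their counterparts in control schools stayed.

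The Statistical analysis section plans to pilot the full-trial analysis, with baseline-adjusted multi-level estimates of the difference between arms. An exclusion that depends on arm, and on the social standing through which the intervention is meant to work, departs from comparison as randomised. A phase III trial could inherit the rule. It would also remove some of the nominated students whom research question 8 and the social network analysis set out to describe.

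**Working it through.** **The plan's own figures.** With six schools, 100–150 students per year group and 85% attending and consenting:

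- 6 × 100 × 0.85 = 510 and 6 × 150 × 0.85 = 765, as the Sample section states.
- The 95% half-width is 1.96 × √(0.85 × 0.15 / N). With N = 600 it is 2.86%, and with N = 900 it is 2.33%, matching the stated ±2.9% and ±2.3%.

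The article gives no figure for the exclusion itself.

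**The sections side by side.**

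| Event | Section | Consequence stated or implied |
|---|---|---|
| Parent opts child out of the study | Recruitment; criterion 4 | Not surveyed, in any school |
| Nominated student declines | Strengths and limitations | Declines the role |
| Parent does not consent to training | Criterion 4 | Excluded from the study |

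The last two rows describe the same practical outcome, a nominee who is not trained, but give it different status. The survey already has its own parental opt-out, so the second limb is not needed to protect families from the survey.

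**Timing.** The order given is baseline, then randomisation, then training. Consent for training would therefore naturally be sought after allocation. This is an inference, because the article does not date that consent.

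**Possible size.** Two inputs are assumptions: the share of the year group invited (10–20%) and the share of those invited without parental consent (5–30%). The fraction removed is the product of the two:

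- Low: 0.10 × 0.05 = 0.5%.
- High: 0.20 × 0.30 = 6%.

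The four intervention schools have 4 × 100 = 400 to 4 × 150 = 600 students on the roll, and at 85% about 340–510 surveyed.

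| | Low | High |
|---|---|---|
| Of the roll | 0.005 × 400 = 2 | 0.06 × 600 = 36 |
| Of those surveyed | 0.005 × 340 = 1.7 | 0.06 × 510 = 30.6 |
| Control schools | 0 | 0 |

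**Illustrative effect on an outcome.** Take participation p = 50%, the 12-month figure cited in the Background. Assume no intervention effect, a fraction f removed, and participation q among those removed. The proportion left in the intervention arm is (p − f·q)/(1 − f). With f = 0.06:

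- q = 30%: (0.50 − 0.018)/0.94 = 51.3%, a shift of +1.3 percentage points and an odds ratio of 1.05.
- q = 70%: (0.50 − 0.042)/0.94 = 48.7%, a shift of −1.3 points and an odds ratio of 0.95.

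The 30–70% range for q is also assumed. With f = 0.005 the shift is 0.1 point.

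**The case against.** The strongest reply is that the literal reading defeats itself. The list mixes schools, students and parents. Read strictly, the second limb would exclude every student whose parent never gave training consent, including all controls and everyone not nominated. The sensible reading is that each limb governs its own activity: opt-out for the study, consent for the training. Recruitment and Strengths and limitations both point that way, and no section describes removing a surveyed student or deleting data for lack of training consent. This stands as to what the authors probably meant. It does not rescue the wording, and no sentence in the article says that such students stay in.

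A second reply is that the article condenses a full protocol and an analysis plan that are not shown, where separate consent procedures may be set out. That is fair as regards anything left out. The point here is a criterion that the article does state, in terms that conflict with its own other sections.

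A reader might also infer three stronger conclusions, none of which the article supports:

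- **That a differential post-randomisation exclusion of material size is established.** The timing is inferred, the rates are assumed, and the illustrated shift is small for a pilot with two control schools and no hypothesis tests.
- **That low uptake of the role would be hidden.** The process evaluation covers feasibility, reach and acceptability, and results are to follow CONSORT for pilot and cluster trials, where exclusions would normally be counted.
- **That the result of progression criterion 5 would change.** Table 2 does not set that criterion by arm. The extreme of 36 students is 36/900 = 4% of the largest roll, and if they complete questionnaires at the same rate as the others the proportion does not move.

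**Conclusion.** The point holds as a wrongly stated eligibility rule. Criterion 4 makes refusal of training a ground for exclusion from the study, in conflict with the route into the survey under Recruitment and with the treatment of refusal under Strengths and limitations. If the rule were applied as written, any loss would fall on the intervention arm alone and among its most-nominated students.

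The likely consequence is modest: 0.5–6% of the intervention cohort against 0% of controls, and at most about 1.3 percentage points on an outcome at 50%. These figures rest on the assumed invitation, non-consent and participation rates. The one-sided direction of the loss needs none of them; it follows from training being offered only in intervention schools. The reason to correct the text is that the rule is wrong in kind and could carry over to a definitive trial.

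**What to change.** Limit criterion 4 to a parent or carer opting the child out of the study. Add a sentence stating that:

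- lack of parental consent for training bars a student only from the peer-supporter role;
- such students stay in the baseline and follow-up survey cohort unless opted out of the study, and are analysed in their school's allocated arm;
- the numbers invited, consented and trained are reported by intervention school as uptake.

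The cost is a short edit to the eligibility text and a matching line in the definition of the analysis population. The abstract describes the surveys as already conducted, so no new survey data are needed. The uptake counts require only a tally of invitations, consents and attendance at training.
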